#### Sham EA control

Participants in the control group will receive sham electro-acupuncture treatment at the same acupoints as the treatment group with a blunt tipped placebo needle named Streitberger placebo needle from Germany [17]. This kind of needle can move inside the handle and appear to be shortened after puncturing without penetrating the skin. Participants will find it difficult to distinguish the placebo needle and real acupuncture needle because of the similar sensation and appearance. The electro-acupuncture device will be connected to points, GV20, GV29, bilateral SP6, and ST36 without any electrical current.

### Outcome measures

The sleep quality will be measured by PSQI scores, data from actigraphy, and dose of hypnotics. Depression symptom is accompanied with insomnia in most patients. So we will adopt PHQ-9 to measure the depression condition in lung cancer patients. QLQ-C30 will be used to assess various aspects related to health, disease, and treatment for cancer patients. The treatment effect will be estimated by these subjective questionnaires and objective data from actigraphy, comprehensively evaluating not only the efficacy of EA on insomnia among lung cancer patients, but also the accompanied symptom and quality of life among cancer patients, which seems more meaningful in clinical practice.

#### Primary outcome measure

The primary outcome will be the mean changes in Pittsburgh Sleep Quality Index (PSQI) in week 8 when compared to the baseline. As the most rigorously validated sleep healthy assessment tool, PSQI is a self-rated questionnaire used to assess sleep quality and disturbance over a 1-month time interval. It consists of 24 items to be rated, 19 of which are self-reported and 5 of which are required secondary feedback from a room or bed partner [18]. The seven components are subjective sleep quality, sleep latency, sleep duration, habitual sleep efficacy (SE), sleep disturbance, use of sleeping medication, and daytime dysfunction. The sum of the individual component scores creates one total score (range 0–21). The higher score indicates a worse sleep quality and more severe sleep disorder and vice versa.

#### Secondary outcome measures

##### Actigraphy

Actigraphy is an objective, non-instrusive method for estimating sleep-wake patterns using activity-based monitoring [19]. Computer-based software is interfaced with devices to provide automatic measurements for certain variables recorded in the actigraphy, such as sleep duration, sleep efficiency, and bedtime onset.

##### Quality of Life Questionnaire Core 30 (QLQ-C30)

Quality of Life Questionnaire Core 30 (QLQ-C30) is designed by the Quality of Life Group from the European Organization for Research and Treatment of Cancer (EORTC), specifically for the purpose of assessing various aspects related to health, disease, and treatment for cancer patients. It is composed of 30 items, divided into five functioning domains, three symptom domains, one domain that evaluates overall quality of life, five single domains, and one separate domain to evaluate financial impact [20]. For the functioning domain and overall quality, the higher scores indicate the better quality of life; conversely, for the symptom domain, a higher score indicates a worse quality of life.

##### Patient Health Questionnaire-9 (PHQ-9)

The Patient Health Questionnaire-9 (PHQ-9), as a 9-item self-administered depression screening and diagnostic tool, is based on the Diagnostic and Statistical Manual of Mental Disorders (DSM-IV) depression symptom criteria. PHQ-9 is used to assess depression conditions during the initial 2 weeks. The final summed scores range from 0 (no depressive symptom) to 27 (all symptoms occurring daily) [21].

#### Other measures

##### Dose of hypnotics

Given participants’ psychological condition, oral intake of hypnotics will be allowed to alleviate their insomnia symptoms. Hypnotics will not be restricted, but the name and dosage of drug must be recorded precisely on CRF, especially when the dosage is increased or decreased.

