
We therefore designed this large-sample multicenter randomized controlled trial with rigorous methods, effective randomization, accurate statistical analysis, and valid measures. We hypothesized that electro-acupuncture is an effective and safe method in treating insomnia among lung cancer patients. The objectives of this trial are:
To evaluate efficacy of electro-acupuncture on insomnia in lung cancer patients as measured by PSQI scores, data from actigraphy, and dose of hypnotics compared with sham EA.To evaluate safety of eletro-acupuncture compared with shame EA by number of adverse events, number of dropout, and the reasons both in treatment group and sham group.To determine whether EA can relieve depression and improve quality of life in lung cancer patients as measured by PHQ-9 scores, QLQ-C30 to compare the between-group difference.

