#### Statistical analysis

A full analysis set (FAS) is based on ITT principle that is including all the qualified participants who meet the inclusion criteria, who receive the intervention at least once, and who provide outcome assessment at least once. In statistical analysis, any the missing primary outcome will be replaced by the data from last time point according to ITT principle. A Per-Protocol Set (PPS) will be used to analyze those who completed the trial without a major violation of the protocol [23]. A Safety Analysis Set (SAS) is based on the principle of exposure to observe safety indicators for any participants received the intervention at least once.

All analysis will be performed in SPSS24.0. Continuous data will be represented by average, standard deviation, median, minimum value, and maximum value through *t* test; rank-sum test is used for ranked data, while chi-square test is adopted to analyze categorical data [24]. (1) Statistical description: Continuous data from week 0 to week 20 will be presented as MD ± SD. *t* test will be used to compare the difference from baseline in both groups and compare variations after intervention between two groups. (2) Equilibrium analysis: To measure the equilibrium at baseline, *t* test or chi-square test is used to compare demographic data and other basic data at baseline, including name, age, marital status, occupation, education, course of disease, pathologic typing of lung cancer, previous treatment of lung cancer, smoking, drinking, tea, coffee, exercise, pain level, other diseases, ECOG score, PSQI score, data from actigraphy, QLQ-C30 score, PHQ-9 score, and dose of hypnotics. Frequency (composition ratio) will be adopted to describe categorical data of two groups at all time points. (3) Safety analysis: all occurred adverse events will be recorded in both groups. Numbers or the incidence rate in the two groups will be analyzed by chi-square test.

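### Hypnotic use is unrestricted and counts in the primary PSQI total, but the stated t test takes no account of it and hypnotic dose has no common unit

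*Protocol article*

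**What the plan says.** All references are to the protocol article.

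- **Dose of hypnotics** (under Other measures): "Hypnotics will not be restricted, but the name and dosage of drug must be recorded precisely on CRF".
- **Primary outcome measure**: "The primary outcome will be the mean changes in Pittsburgh Sleep Quality Index (PSQI) in week 8 when compared to the baseline". The total is the sum of seven components and runs from 0 to 21. The list of components ends with "sleep disturbance, use of sleeping medication, and daytime dysfunction".
- **Background, first objective**: efficacy is to be judged "as measured by PSQI scores, data from actigraphy, and dose of hypnotics compared with sham EA". The opening of Outcome measures likewise names hypnotic dose as one of three measures of sleep quality.
- **Statistical analysis**: a t "test will be used to compare the difference from baseline in both groups and compare variations after intervention between two groups". The only mention of hypnotics in that section is at the end of the list of variables checked for baseline balance: "PHQ-9 score, and dose of hypnotics".
- **Table 1**: hypnotic dose is recorded at weeks 0, 1, 4, 8, 12 and 20.
- **Abbreviations**: ANCOVA is listed, but no analysis of covariance appears in the methods.

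**The concern.** A patient's hypnotic use reaches the primary score by two routes. Taking more raises the sleeping-medication component directly. It may also lower other components, since the Background credits drug treatment with a good short-term effect. Both routes end in the same total, and the t test on change cannot separate them.

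This affects what the result can be used to say. The Discussion wants to know whether real electro-acupuncture is what helps, beyond placebo. Suppose EA patients cut their hypnotics and sleep about as before, or sham patients raise theirs and sleep better. The total would move in either case, and the planned analysis would give no means of telling why.

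The second difficulty is hypnotic dose as an outcome. The Background names several agents from two drug classes. A mean of recorded dosages across different drugs is not on a common scale, so the comparison would depend on which drugs happened to be prescribed.

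**Working it through.** **1. The plan's own figure.** Inputs from Sample size estimation: difference 2.0, SD 4.36, two-sided 5%, power 90%, dropout 20%.

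- Normal approximation: n per arm = 2 × (1.960 + 1.282)² × 4.36² / 2.0² ≈ 99.9, so 100 per arm (200 in total).
- Exact two-sample t test (noncentral t): 101 per arm (202 in total), power 0.9005. This reproduces the stated 202.
- Dropout: 202 / (1 − 0.20) = 252.5, against 252 stated. The difference is rounding only.

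The sample size is not in dispute. It supplies the scale for what follows.

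**2. What the total contains.** Write the between-arm difference in PSQI change as

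difference in total = difference in the medication component + difference in the other six components.

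Assuming seven equally weighted components, each spans 21 / 7 = 3 points. Randomisation makes the arms comparable at baseline on average, so the medication component can separate them by at most 3 points at week 8. The assumed effect on the total is 2.0. The ceiling therefore does not rule out a material contribution, but a ceiling is not an estimate.

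**3. Range under assumption.** The document gives no rates of hypnotic use, so the shares below are assumptions. Each takes the extreme move from no use to the top category and allows no offset through the other components.

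| Extra share of sham patients making that move | Shift in PSQI difference | Relative to 2.0 |
|---|---|---|
| 10 percentage points | 0.10 × 3 = 0.3 | 15% |
| 20 percentage points | 0.20 × 3 = 0.6 | 30% |

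Better sleep on the drug would act in the opposite direction by an unknown amount. The table shows how the component works. It does not measure a bias.

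**4. If the net effect were to narrow the difference.** With 101 per arm and SD 4.36, power by the noncentral t is as follows. The narrowed values are assumptions too.

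| Observed difference | Power |
|---|---|
| 2.0 | 90% |
| 1.75 | 81% |
| 1.5 | 68% |
| 1.0 | 37% |

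**5. Where the stated tests touch hypnotic dose.** Statistical analysis describes continuous data from week 0 to week 20 and compares them by t test. Among the efficacy outcomes in Table 1, only PSQI and hypnotic dose are measured over that whole span; actigraphy, QLQ-C30 and PHQ-9 are taken at weeks 0 and 8 only. Read as written, the t test therefore covers hypnotic dose if dose is treated as continuous. The case report form holds drug name and dosage, so a conversion is possible, but the article states none.

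**The case against.** **The analysis plan may cover it.** Covariates, sensitivity analyses and dose conversion are often left to a statistical analysis plan, which is not shown. That limits the point: their absence from an article is not in itself a fault. What remains is that the article fixes an unadjusted t test on change for an outcome that contains medication use, and names hypnotic dose as an efficacy measure under tests that need a common scale.

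**An effect with hypnotics as used is legitimate.** It is. Less medication can be part of the benefit that PSQI measures, and the assumed 2.0 is itself a PSQI difference. The article does not, however, say that this is the effect it targets. Actigraphy carries no medication item and helps, but it too is recorded under whatever hypnotics patients take.

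**Stronger readings that the document does not support.**

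- *Hypnotic use could create a false EA effect.* If EA did nothing, a shift of 0.5 or 1.0 point would be declared significant about 13% or 37% of the time. That needs hypnotic use to differ between arms without any treatment effect. Patients are randomised, patients and assessors are blinded, and the acupuncturists are not told hypnotic dose, so the design gives no reason to expect such a shift.
- *The result is biased in a known direction.* The two routes oppose each other, and nothing in the document shows that hypnotics improve all six other components.
- *The plan says raw milligrams will be averaged.* It does not. This follows only if the t test is applied to recorded dose with no conversion.
- *The outcome's status is contradictory.* Table 1 places hypnotic dose below the Secondary outcomes header and the text places it under Other measures. The same part of the table also holds adverse events, credibility and blinding, so this may be layout.

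**A week-0 covariate does not address later changes.** Correct, and the fix says so.

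**Conclusion.** The point holds as one of interpretation. The planned PSQI comparison validly estimates EA versus sham with hypnotics as used, but cannot apportion the difference between changed medication use and better sleep. The size and direction of the medication part are unknown. The one bound available is 3 of 21 points, and it rests on equal component weights. The shares and narrowed differences in the working are illustrations on assumed values.

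For hypnotic dose as an efficacy measure, the t test applied as written to different drugs would not give an interpretable comparison. This assumes that no conversion is set out in a plan not shown. The status of the outcome is a minor clarification. The changes are worth making because they cost little and bear on the primary result.

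**What to change.** Leave the rule on hypnotics unchanged and amend the analysis.

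1. Replace the primary t test with a model for PSQI at week 8 adjusted for baseline PSQI and week-0 hypnotic use. State that this handles baseline differences and precision only, not changes in hypnotic use after randomisation.
2. Pre-specify a sensitivity analysis of PSQI without the sleeping-medication component, reported beside the total. It removes that item's direct contribution, but not any effect of the drugs on the other components. Describe the primary effect as EA versus sham with hypnotics as used.
3. Analyse hypnotic use on one common scale, such as standardised dose units, or as decreased, unchanged or increased, using the rank-sum test that the article already provides for ranked data.
4. Give hypnotic dose one status across the objectives, Table 1 and Other measures.

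The cost is a few sentences, a conversion table if dose units are chosen, and a little more analysis. Week-0 hypnotic use, later doses and the PSQI components are already collected, so no new data are needed.

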##### Assessment of safety

Any adverse events (AEs) will be observed, those which are deemed to be unfavorable or unintended signs, symptoms, or diseases occurring due to the acupuncture or the hypnotics intake should be dealt with according to the protocol. The type of AEs and severity will be recorded in the CRF, including continuous needling pain, local hematoma, infection, discomfort, palpitation, or dizziness during and after the treatment. If a severe adverse event (SAE) occurs, they should be reported to the researchers and the Ethics Committee in detail within 24 h after the occurrence and be assessed by the Treatment Emergent Symptom Scale (TESS) for further evaluation and management. And then the Ethics Committee will deliver the solution to DSMB, who retain the right to terminate the trial at any point. Researchers will pay sustained attention to participants who experience any AEs until it has been resolved, especially to those who have withdrawn the trial due to the AEs.

##### Assessment of credibility

In this trial, the credibility assessment questionnaire [22] is particularly applied to assess the reliability and credibility in the controlled trials of acupuncture and other physical therapies. The questions presented to the participants for rating on a 6-point scale are as follows: 1. How confident do you feel that this treatment can alleviate your complaints? 2. How confident would you be in recommending this treatment to a friend who suffered from similar complaints? 3. How logical does this treatment seem to you? 4. How successful do you think this treatment would be in alleviating other complaints?

##### Assessment of the subject blinding success rate

All participants will receive the blinding test twice in week 1 and week 8 to assess the success rate of subject blinding. The question is “When you are volunteered for the trial, you were informed that you have the equal chance of receiving traditional acupuncture and acupuncture-like stimulation treatment. Which one do you think you have received?” Participants should choose one of the three answers: acupuncture treatment, acupuncture-like stimulation treatment, or uncertain.

### Statistical methods

#### Sample size estimation

The calculation of sample size is based on the review of acupuncture for insomnia [10]. Referring to this study, the mean difference of PSQI between two groups is assumed to be 2.0 with standard deviation of 4.36 for the both groups. Through PASS system (version 15.0.5) calculating, a sample size of 202 can provide 90% power to reject the null hypothesis with a significance level of 0.05 using a two-side two-sample T-tests assuming equal variance. Considering the expected dropout rate of 20%, the final sample size is 252, 126 for each group.

#### Data collection and management

Data will be collected in the CRF by the assessors after acquiring the signed consent from participants. To guarantee the consistency of data, two research coordinators will double-enter and check data from CRF once a week. To promote participants retention, and prevent their loss, assessors will make phone calls during a 3-month follow up.

#### Statistical analysis

A full analysis set (FAS) is based on ITT principle that is including all the qualified participants who meet the inclusion criteria, who receive the intervention at least once, and who provide outcome assessment at least once. In statistical analysis, any the missing primary outcome will be replaced by the data from last time point according to ITT principle. A Per-Protocol Set (PPS) will be used to analyze those who completed the trial without a major violation of the protocol [23]. A Safety Analysis Set (SAS) is based on the principle of exposure to observe safety indicators for any participants received the intervention at least once.

All analysis will be performed in SPSS24.0. Continuous data will be represented by average, standard deviation, median, minimum value, and maximum value through *t* test; rank-sum test is used for ranked data, while chi-square test is adopted to analyze categorical data [24]. (1) Statistical description: Continuous data from week 0 to week 20 will be presented as MD ± SD. *t* test will be used to compare the difference from baseline in both groups and compare variations after intervention between two groups. (2) Equilibrium analysis: To measure the equilibrium at baseline, *t* test or chi-square test is used to compare demographic data and other basic data at baseline, including name, age, marital status, occupation, education, course of disease, pathologic typing of lung cancer, previous treatment of lung cancer, smoking, drinking, tea, coffee, exercise, pain level, other diseases, ECOG score, PSQI score, data from actigraphy, QLQ-C30 score, PHQ-9 score, and dose of hypnotics. Frequency (composition ratio) will be adopted to describe categorical data of two groups at all time points. (3) Safety analysis: all occurred adverse events will be recorded in both groups. Numbers or the incidence rate in the two groups will be analyzed by chi-square test.

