**Method:**

This is a protocol for a multicenter randomized single-blinded sham-controlled trial. We will randomly assign 252 eligible patients with lung cancer-related insomnia into two groups at a ratio of 1:1, the treatment group (EA) and the control group (sham EA). All treatment will be given 3 times per week for 8 weeks, and a 12-week follow-up will be conducted. The primary outcome will be measured by the Pittsburgh Sleep Quality Index (PSQI). The secondary outcomes will include sleep parameters recorded from the actigraphy, scores from Quality of Life Questionnaire Core-30 (QLQ-C30), and Patient Health Questionnaire-9 (PHQ-9). All adverse effects during the trial will be assessed by the Treatment Emergent Symptom Scale (TESS). All analyses will be based on ITT principle and performed with the statistical software SPSS (version 24.0) by *t* test, rank-sum test, chi-square, and so on. A two-sided significance level will be set at 5%.

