Although this trial is designed to address the limitations in previous trials, there still remain potential challenges waiting for us to solve. Firstly, to ensure the successful implementation of protocol, acupuncturists will accept training before the beginning of the trial and prepare to reasonably dispose of patients through systematically studying and mastering detailed protocol, particularly in terms of the manipulation of EA and sham acupuncture device and measurement questionnaires. Secondly, to achieve adequate participant enrollment to target sample size in time, the patients will be recruited from three hospitals in Shanghai: Shanghai Municipal Hospital of Traditional Chinese Medicine (TCM), Shanghai Chest Hospital, and Putuo District Central Hospital, which are all comprehensive hospitals with numbers of lung cancer patients on a daily basis. Oncologists in these hospitals have joint this trial, and they will be responsible to introduce this research to eligible patients and recruit them. We also have made some leaflet, billboard inside hospitals, and recruitment link on the Internet to attract patients’ attention. Thirdly, to ensure compliance from patients and ensure minimal loss to follow-up, we will use the following strategies. Clinical trial publicity brochures will be handed out to all hospitals to popularize clinical trial knowledge. Before assigning informed consent, detailed attentions should be explained to participants, including trial protocol and intervention demands, positive effects, and potential adverse events. After fully consideration, they can assign the informed consents. Besides, we will strengthen the public education of medical knowledge to patients, care for the patients, and improve their quality of life in all relevant aspects. For instance, we will make reasonable arrangements for treatment time and consultation time by phone or e-mail to increase their attendance rate. Besides, free acupuncture treatment will be promised by acupuncturists if the patients are not satisfied with the results of their treatment during the trial [26]. And participants will get adequate transportation allowance if they have completed all the treatment and follow-up. What is more, more flexible methods will be adopted to measure patients during the follow-up period, like calling to ask the questions or making an electronic edition of PSQI through message or other communication software. We have successful recruiting experience in our previous studies related to insomnia whose dropout rates were all low. Therefore, we are confident that we will have low dropout rate in this trial.

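### Carrying the last PSQI forward to week 8 can bias the primary comparison and lower its power, and the ITT principle does not call for it

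*Protocol article*

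**What the plan says.** The Primary outcome measure section fixes the endpoint: "The primary outcome will be the mean changes in Pittsburgh Sleep Quality Index (PSQI) in week 8 when compared to the baseline". Table 1 lists PSQI at weeks -1, 0, 4, 8, 12 and 20.

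For missing values, the Statistical analysis section states that "any the missing primary outcome will be replaced by the data from last time point according to ITT principle". It names a per-protocol set but no other way of handling missing data.

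The same section describes the full analysis set (FAS) as ITT-based. It limits the set to participants who meet the inclusion criteria, "who receive the intervention at least once, and who provide outcome assessment at least once". It does not say whether the baseline PSQI counts as an outcome assessment. The abstract says "All analyses will be based on ITT principle".

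The Sample size estimation section assumes that "the mean difference of PSQI between two groups is assumed to be 2.0", "with standard deviation of 4.36 for the both groups", which gives 202 patients for 90% power. It then adds: "Considering the expected dropout rate of 20%, the final sample size is 252, 126 for each group".

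**The concern.** A patient without a week-8 score is analysed as if the score had stayed where it was at the last visit. Scores may well move between that visit and week 8. Entry requires a PSQI above 11, which invites regression to the mean, hypnotics are unrestricted, and both arms receive 24 sessions (3 per week for 8 weeks). The carried score then misses part of the change, and the filled-in value is treated as observed.

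If the arms lose equal proportions, the lost change dilutes the treatment effect. If they lose unequal proportions, improvement common to both arms becomes an apparent difference between them, in whichever direction the dropout gap points. The rule is therefore not reliably conservative.

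Two further points bear on the same text. The sample size treats the 20% as gone from the analysis, while the rule keeps them in with earlier scores. And the set called ITT-based is not all randomised patients.

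**Working it through.** **Inputs from the protocol.** Difference 2.0, SD 4.36, two-sided alpha 0.05, t test, 202 evaluable, 20% dropout, 126 per arm. **Assumptions, not in the protocol:** all 20% are lost before week 8; dropouts would otherwise have scored like completers; the share of the effect present in carried values, the improvement within each arm and any dropout gap are as stated at each step.

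**1. The plan's own figure.** A noncentral t test with 101 per arm (202 in total) gives 90.05% power. Then 202 / 0.8 = 252.5, which agrees with 252. The design reproduces, with dropouts counted as lost.

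**2. Bias of the rule.** Let d be the proportion carried in an arm and g the mean improvement in that arm between the carried visit and week 8. The analysed arm mean falls short by d × g, so

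bias in the EA-minus-sham improvement = d(sham) × g(sham) − d(EA) × g(EA).

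With equal dropout this is zero only if g is the same in both arms, that is, if the carried arm difference equals the week-8 difference. With unequal dropout, a shared g is enough to create bias.

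**3. Equal dropout.** With d = 0.20 and a fraction f of the effect present in the carried values, the expected difference is 2.0 × (0.8 + 0.2f). The standard error is 4.36 × √(2/126) = 0.549. Power by noncentral t:

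| f | Expected difference | Power |
|---|---|---|
| 0 (all carry baseline) | 1.6 | 82.7% |
| 0.25 | 1.7 | 86.9% |
| 0.5 | 1.8 | 90.4% |
| 0.75 | 1.9 | 93.1% |
| 1 | 2.0 | 95.2% |

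Power falls below 90% when f is below about 0.47 or, with baseline carried, when dropout before week 8 exceeds about 11%. Zero changes also alter the spread. If the SD in each arm is recomputed as √[(1−d) × 4.36² + d(1−d) × m²], with m the arm's improvement, the baseline-carried power is 89% to 79% for assumed sham improvements of 0 to 5 points.

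**4. Unequal dropout with a true effect.** Assume improvements of 5 (EA) and 3 (sham), with baseline carried:
- EA 10%, sham 30%: 0.9 × 5 − 0.7 × 3 = 2.4.
- EA 30%, sham 10%: 0.7 × 5 − 0.9 × 3 = 0.8.

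**5. Unequal dropout with no true effect.** Assume 3 points of improvement in both arms and baseline carried. The false difference is the dropout gap × 3:

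| Dropout gap | False difference | Type I error |
|---|---|---|
| 10 points | 0.30 | 8.5% |
| 15 points | 0.45 | 12.9% |
| 20 points | 0.60 | 19.3% |

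If week 4 is carried instead and already holds half the improvement, these differences halve. A 20-point gap then gives 0.30 and 8.5%.

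**6. Two readings of the FAS.** If baseline counts as an outcome assessment, the outcome condition removes almost nobody and early losses carry baseline (f = 0 in step 3). If a post-baseline score is required, early losses are excluded and only week 4 can be carried. With 10% excluded and 10% carrying week 4, power by normal approximation is 86.7%, 88.6% and 90.4% for f = 0, 0.25 and 0.5. If all 20% are excluded and the effect is unchanged, about 201.6 patients remain and power is 90.3% on the same approximation.

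**The case against.** **Certain bias.** A reader might infer that the estimate is bound to be biased and the planned power bound to be lost. The protocol does not support that. It gives no figures for change by week 4, for the timing of dropout or for dropout by arm. If week-4 values already hold about half the effect, power stays at 90%; if they hold all of it, power is above plan. The 20% may include losses between weeks 8 and 20, which do not touch the primary endpoint, and the Discussion expects low dropout. This stands, and it makes the size of the problem conditional. The planning figure is still 20%.

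**Type I error.** The 19% needs a 20-point gap, a 3-point shared improvement and baseline carried. The sham needle is designed to look and feel similar and patients wear eye-patches, so a large gap is not a given. This also stands: the figures are a worst case.

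**Both faults at once.** It is tempting to say that early dropouts are scored as unchanged and are also excluded. These need opposite readings of the outcome condition and cannot both hold for the same patients.

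**The ITT label.** The abstract and the analysis section use the same loose phrase, and neither expressly promises all randomised patients. Envelopes are opened only at the first treatment, so leaving out never-treated patients cannot depend on a known allocation. Exclusion alone does not cost the planned power. What remains is that the outcome condition acts after allocation is revealed and can select patients differently by arm.

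**Left to the analysis plan.** Detail of this kind often sits in a separate plan. Here, however, the protocol itself fixes the rule for the primary outcome and gives a wrong reason for it.

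**Conclusion.** The point holds in conditional form. The rule is fixed for the primary outcome and ITT does not justify it. It biases the comparison unless the improvement missed by carrying scores forward, weighted by dropout, happens to balance between arms.

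At 20% dropout before week 8, SD 4.36 and a true effect of 2.0, equal dropout gives power from about 83% to 95% against the planned 90%. Under unequal dropout the bias can run either way. In the assumed worst case, type I error reaches about 8.5% to 19%. The possibility of a false positive is the more serious half, because it removes the usual defence that the rule is conservative.

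The FAS is narrower than all randomised patients although it is called ITT-based. Its outcome condition carries a risk of selection bias, not a loss of planned power. Whether baseline counts as an outcome assessment decides which value is carried and needs to be stated.

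**What to change.** Delete the carry-forward rule and define the primary analysis set as all randomised patients in their allocated arm. Then use one of the following:

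- A likelihood-based repeated-measures model with PSQI at baseline, week 4 and week 8 as responses, the baseline mean constrained equal across arms, adjusted for hospital, with the week-8 arm contrast primary. Baseline must be a response: if it is only a covariate, patients with no later PSQI contribute nothing and the analysis is again not of all randomised patients.
- Multiple imputation using baseline PSQI, week-4 PSQI and hospital.

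Both assume that missingness is explained by the data in the model, so add a delta-adjusted or control-based sensitivity analysis. If a restricted set is kept as well, label it as such and say whether baseline counts as an outcome assessment.

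Reduce the missing data too. The Discussion already says that "more flexible methods will be adopted to measure patients during the follow-up period, like calling to ask the questions"; extend this to week 8 for patients who stop attending.

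**Cost.** Modest extra analysis work, no extra patients, and up to about 50 remote contacts at week 8 (0.20 × 252 = 50.4). The change should be made before unblinding.
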